### Sample for quasi-phase II pilot arm

In the absence of any data on the unguided i-RFCBT, no power and sample size calculation was conducted for this arm. We will therefore aim to recruit the same number of participants for this arm as the other arms (n = 78), giving a total sample size of 234. The inclusion of this intervention arm is to explore the feasibility of this unguided intervention with respect to attrition, acceptability and estimates of incident rate and effect size.

### Interventions

#### Guided i-RFCBT

The guided intervention is an English version of i-RFCBT (called MindReSolve). RFCBT is derived from theoretical models [11] and experimental findings, which propose the existence of distinct types of repetitive thought (RT) with distinct consequences: constructive RT is characterized by a concrete, specific and action-oriented mode of processing, focusing on how events happen, whereas unconstructive RT is characterised by an abstract and evaluative processing mode, focusing on the meaning and implications of events and difficulties [11]. In experimental studies, relative to the abstract mode, the concrete mode improved problem-solving [53, 54] and reduced emotional reactivity in response to failure [55]. Underpinning RFCBT is the idea that shifting individuals into the concrete mode will reduce unconstructive rumination; consistent with this, repeated training of dysphoric and depressed participants to become more concrete reduces depression and rumination in both a proof-of-principle study and a randomised controlled trial [31, 33]. RFCBT therefore involves experiential and imagery exercises to adaptively shift processing mode (including concreteness, absorption and compassion), as well as functional analysis to help patients spot when rumination starts, distinguish between helpful versus unhelpful RT, and learn more functional responses. RFCBT seeks to change the process of thinking as opposed to the content of thoughts as in standard CBT [30]. In addition, rumination is conceptualised as a form of avoidance [11, 56], which is targeted on behavioural activation principles [57] with avoidance behaviour being replaced with more appropriate approach behaviours.

I-RFCBT consists of six modules, each taking around an hour to complete in session and 1 to 2 weeks to practise. It includes psycho-education, mood diaries, on-line experiential exercises using audio-recordings, pictures and video vignettes of students’ experiences of the therapy. The modules each follow the same basic structure: reflection on the previous session, introduction of a new technique, practical exercises and planning how to practise or implement the technique in daily life. The specific behaviour-change techniques are drawn from the following groups in the BCT Taxonomy (v1) [58]: goals and planning (goal setting, action planning, review behaviour and behavioural contract), feedback and monitoring (self-monitoring of behaviour and outcomes), shaping knowledge (information about antecedents), natural consequences (information about social and environmental consequences and monitoring of emotional consequences), associations (prompts/cues and associative learning), repetition and substitution (behavioural practice/rehearsal, behaviour substitution, and habit formation), antecedents (restructuring physical and social environment, avoiding/reducing cues for the behaviour), and self-belief (mental rehearsal of successful performance, focus on past success, and self-talk). The key strategies include coaching participants to spot warning signs for rumination and worry, and then to make IF-THEN plans in which an alternative strategy is repeatedly practised in response to the warning signs. These strategies include being more active, slowing things down, breaking tasks down, opposite action, relaxation, concrete thinking, becoming absorbed, self-compassion and assertiveness.

The intervention is accessed through a secure website, with each participant having a password protected account. Participants’ log-ins are automatically recorded by the programme, allowing for an automated measure of treatment compliance. Reminder emails will be sent to participants after 2 weeks if they have not completed the module.

The participant can work through each module at his own pace but can only move from one module to the next after the coach has provided feedback. The coach will provide feedback on these responses within 2 working days, in particular highlighting any positive steps made and encouraging participants to sustain these as well as pointing out areas to focus on over the next module. Participants will also be able to send questions to their assigned therapist throughout the programme if they are having difficulty with a specific exercise.

The intervention will be supported by qualified clinicians who have received specific training in the rumination-focused CBT approach. Treatment fidelity is ensured through the use of fixed modules in the platform, ensuring that all participants receive identical content. Detailed template responses for each module provide the coach with constrained feedback faithful with the treatment model, which they can then tailor to individual client responses. All responses from both the client and coach are automatically saved by the online platform, and a random sample will be checked against the templates to ensure they are faithful to the treatment. Furthermore, coaches will be provided with ongoing supervision with the developer of RFCBT to encourage fidelity. Supervision meetings will involve a brief overview of all clients and a more in-depth discussion of cases deemed to be more complex or where there is risk or non-response to the intervention.

#### Unguided i-RFCBT

The unguided version of the therapy contains the same six modules as the guided version, with almost identical content, adapted for self-help, including some conditional feedback on common difficulties with exercises. Participants are able to move freely from one module to the next, but are advised to spend 1 to 2 weeks on each to allow time for practice. Participants in the unguided version will be made aware that there is no coach monitoring their responses. However, they will be told that their questionnaire scores will be monitored on a weekly basis to check for any risk reported.

### Control condition

Participants in the control condition will be informed that they have been allocated to carry on as usual. In order to ensure participants’ welfare, participants are permitted to access any other treatments throughout the course of the study, as necessary. They will also be able to access the unguided i-RFCBT at the end of the study if they so wish.

### Blinding

This is a single blind study, with the researcher conducting outcome measures while blind to allocation. Participants will be asked at the end of the screening interview not to disclose their allocation to the researcher in any of their future correspondence with the researcher and reminded of the importance of this prior to and during each follow-up interview. Due to the intervention, participants and therapists cannot be blinded.

### Follow-up assessments and outcome measures

The primary outcome of interest of this study is the onset of a major depressive episode over a 12-month period, which we will assess with the SCID-I at 3 (post-intervention), 6 and 15 months after randomisation. The use of the SCID-I will allow for the ascertainment of depressive episodes that may have occurred between assessments (continuous time-to-onset and occurrence) and will also enable us to assess clinically significant symptoms of anxiety (particularly generalized anxiety disorder) that may have arisen in isolation or comorbid with depression. The severity of the depressive symptoms is measured using the PHQ-9 and of the anxiety symptoms using the GAD-7. The effect of the intervention on levels of worry and rumination will be assessed using the PSWQ and RRS. A number of potential confounding variables are also measured: stressful life events, using the Episodic Life Event Interview and any treatments received outside the trial (medication, therapy and use of self-help materials). Each assessment will take place via a telephone interview, with the option of the questionnaire measures being returned by email or post. To increase participant retention and completion of follow-ups, multiple attempts and multiple means (email, telephone and post) will be used to contact participants. Additionally, to increase motivation to complete the follow-up measures, lottery draws for £50 in vouchers will be held, with each participant receiving one ticket per completed follow-up.

### Feasibility and acceptability outcome measures (quasi-phase II pilot arm)

With respect to the unguided intervention, feasibility and acceptability of data collection procedures, levels of attrition, effect size and acceptability of the unguided internet RFCBT intervention will be measured to aid planning for a fully powered, definitive, phase III trial. The feasibility of data collection procedures will be assessed by measuring the missing items on the clinical outcome measures, the number and timing of drop-outs and whether these vary across arms. The acceptability of the intervention will be assessed using a behavioural index, which will measure the number of modules completed, the time spent logged into the site and which modules are completed more easily or frequently than others.

### Statistical analysis plan for phase III efficacy trial

Data cleaning will follow the protocol set out by Tabachnick and Fidell [59]. Statistical analysis will follow the CONSORT standards [60]. Unplanned missing data will be handled via multiple imputation (MI). Sensitivity analysis, assuming a variety of MI models (Missing at Random; Missing Not at Random), will verify the likely impact of missing data. Auxiliary variables will be used to improve the estimation of missing data. Primary analyses will be conducted on the intention-to-treat (ITT) sample.

Subsequent analyses will use the Complier Average Causal Effect (CACE) analysis [61, 62]. CACE assumes that randomisation has no direct effect on outcome variable; instead it assumes that the effect of treatment depends on the compliance to treatment (operationalized in terms of completing four out of six modules), which in turn is dependent on randomisation. Therefore, CACE provides estimates of a treatment effect whilst taking into account adherence and compliance with the treatment and whilst also retaining the benefits of randomisation. This model is thus an exemplar of using an Instrumental Variable (IV) where randomisation is the instrument, which is correlated with compliance to the treatment, and directly unrelated to the outcome. In simple terms, CACE finds the difference in the outcome variable between the compliers in the treatment arm and the compliers in the control arm had they been offered the treatment, assuming that the rates of compliance are similar in both arms as a consequence of randomisation.

As a prevention study, the main outcome of interest is the occurrence and time to onset of any depressive episode. Cox regression survival analyses will be performed to examine the effect of the preventive intervention on episode onsets of major depression. Participants will be censored upon measurement dropout or end of study. Although condition will be the main independent variable included in the model, we will also consider sex and history of past depression (the stratification variables).

The secondary outcome of occurrence/time to onset of generalized anxiety disorder will also be assessed using Cox regression survival analyses. Symptom severity and levels of rumination/worry will be examined using mixed model ANCOVAs: between group (ITT/CACE) and repeated measures (3 to 15-month follow-ups), with baseline symptom levels and stratification variables as covariates.

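### The CACE analysis counts completers of one to three modules as untreated, so it overstates the complier effect to the extent that partial completion helps

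*Protocol article*

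**What the plan says.** The section on the statistical analysis plan for the phase III efficacy trial makes intention-to-treat (ITT) the primary analysis and CACE a subsequent one. It states the identifying assumption openly: "CACE assumes that randomisation has no direct effect on outcome variable". It describes the design as an instrumental-variable model in which "randomisation is the instrument, which is correlated with compliance to the treatment, and directly unrelated to the outcome". The variable that must carry the whole effect is compliance, "operationalized in terms of completing four out of six modules". The section gives no other threshold and no dose-based version.

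The section on guided i-RFCBT describes what a participant receives below that threshold. "I-RFCBT consists of six modules, each taking around an hour to complete in session and 1 to 2 weeks to practise". All modules share a structure of "reflection on the previous session, introduction of a new technique, practical exercises and planning how to practise or implement the technique in daily life". A participant "can only move from one module to the next after the coach has provided feedback". Log-ins are "automatically recorded by the programme, allowing for an automated measure of treatment compliance".

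Of the control arm, the section on the control condition says: "They will also be able to access the unguided i-RFCBT at the end of the study if they so wish".

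**The concern.** For an instrumental-variable estimate to be valid, the offer of the programme must change nothing for participants whose compliance variable stays at zero. With the cut at four modules, that group includes everyone who completes one, two or three. A three-module participant has had half the programme: about three hours in session and three to six weeks of practice, with coach feedback before at least the second and third modules. A one-module participant has had about one hour and one to two weeks of practice.

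The trial's premise is that these techniques work. It is hard to reconcile that premise with exactly zero effect below four modules, and the article gives no reason for expecting it. Any effect in the partial completers enters the ITT difference, but those participants are left out of the denominator that rescales it. At stake is the only adherence-adjusted estimate the article plans. The article presents that estimate as keeping the benefits of randomisation and gives no caveat about the threshold.

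**Working it through.** The article states no compliance rate and no CACE figure, so there is nothing to reproduce. The check is of the mechanism, followed by a range.

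**Inputs from the article**
- Cut-off: four of six modules (statistical analysis section).
- Control access to the programme: only at the end of the study (control condition section), so no control participant is taken to receive it during follow-up.
- Planning rates: 32.2% control and 13.1% guided (sample size section). Risk difference = 32.2 − 13.1 = 19.1 points, used here as an illustrative ITT effect.
- Planning symptom effect: d = 0.51 (same section).

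**Assumed inputs, not in the article**
- c, the share completing four or more modules.
- p, the share completing one to three.
- f, the benefit of partial completion as a fraction of the complier effect.
- Three pairs of shares completing at least four / at least one module: 50%/80%, 60%/85% and 70%/90%. These give p = 0.30, 0.25 and 0.20.

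**Formula**
1. With no control access, the simple estimator is CACE = ITT / c.
2. If partial completers benefit by f times the true complier effect T, then ITT = (c + f·p)·T.
3. Dividing, CACE / T = (c + f·p) / c = 1 + f·p/c.

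The ratio is 1 if f = 0 or p = 0, above 1 if f > 0, and below 1 if f < 0.

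**Simulation check** (4 million subjects, c = 0.6, p = 0.2, T = 0.200)

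| f | Formula | Simulated estimate |
|---|---|---|
| −0.25 | 0.183 | 0.183 |
| 0 | 0.200 | 0.200 |
| 0.5 | 0.233 | 0.233 |
| 1 | 0.267 | 0.268 |

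**Overstatement, f·p/c**

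| At least four / at least one | p/c | f = 0.25 | f = 0.5 | f = 1 |
|---|---|---|---|---|
| 50%/80% | 0.30/0.50 = 0.600 | 15% | 30% | 60% |
| 60%/85% | 0.25/0.60 = 0.417 | 10% | 21% | 42% |
| 70%/90% | 0.20/0.70 = 0.286 | 7% | 14% | 29% |

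**Middle row, in points of risk.** The four-of-six estimate is 19.1/0.60 = 31.8. The true complier effect would be:
- f = 0: 31.8
- f = 0.25: 19.1/(0.60 + 0.0625) = 28.8
- f = 0.5: 19.1/(0.60 + 0.125) = 26.3
- f = 1: 19.1/0.85 = 22.5

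**Middle row, symptom scale, f = 0.5.** The estimate is 0.51/0.60 = 0.85 against a true 0.51/0.725 = 0.70, the same 21%.

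**The case against.** A reader might infer that the four-module cut simply breaks the instrumental-variable assumption and makes the complier effect too large. The documents do not support that. Both the violation and its direction require that partial completers exist and that they benefit. The article reports no completion rates and no effect by number of modules. If one to three modules do nothing, there is no bias. If they harm, the bias runs the other way: at c = 0.6, p = 0.2 and f = −0.25 the estimate is about 8% too small (0.183 against 0.200).

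Four further objections have force.

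- The largest figures, 60%, 42% and 29%, need a single module to work as well as four or more. They are ceilings, not expectations.
- The ratio estimator is an illustration. Onset is to be analysed by Cox regression, and the article names CACE explicitly only with the mixed-model analyses of symptoms, rumination and worry. The size of the bias in the planned models would differ in form.
- The cut was set in advance and its assumption stated openly. Lowering it changes the question to the average effect among all starters. That equals the effect in four-module completers only at f = 1, so it is not a corrected value of the same quantity.
- A cut at one completed module still counts as untreated someone who begins the first module without finishing it. Defining exposure as starting a module leaves less of this problem.

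These points rule out simply replacing the four-of-six definition. They do not remove the tension between the zero-effect requirement and the article's own description of each module, and they do not count against reporting a second version alongside.

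**Conclusion.** The point holds conditionally. To the extent that one to three modules are beneficial, the stated no-direct-effect assumption is violated and the complier effect is overstated by a factor of about 1 + f·p/c. Under the three assumed pairs of completion rates this is 7% to 15% at f = 0.25, 14% to 30% at f = 0.5, and no more than 29% to 60% at f = 1. These sizes rest on assumed values of c, p and f, on no control access to the programme during follow-up, and on a simple difference scale.

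The primary result is not in doubt, although a reader might extend the point to it. ITT is primary, and neither it nor the sample size depends on the compliance definition. Only the subsequent CACE results are affected. The change is still worth making, because the possible bias is foreseeable and this is the only adherence analysis planned.

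**What to change.** In the statistical analysis section, keep the four-of-six CACE but prespecify a second CACE to be reported beside it. Exposure in the second should be either any exposure (at least one module started or completed) or the number of modules completed, 0 to 6. State that the four-of-six estimate is an upper bound on the complier effect if partial completion is beneficial. Report the shares completing none, one to three, and four or more modules, so that readers can judge p/c.

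The cost is one extra analysis on data the platform already logs; the primary analysis does not change. Each alternative has a price. The any-exposure version estimates the average effect among all starters, not the effect of completing four or more modules. The module-count version assumes a linear dose effect.

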### Randomisation and allocation concealment

Independent computer-generated block randomisation to the guided i-RFCBT, unguided i-RFCBT or the no-intervention control group will be used. Randomisation will be stratified by sex and by past history of depression (presence or absence of past depressive episodes) to assess the effect of sex on outcomes and to examine potential differences between prevention of first onset and relapse prevention. The randomisation uses blocks of three to ensure close parity of randomisation across the intervention arms across time. Because of the two levels of stratification by sex and by level of depression, with blocks of three, the researcher would not be able to anticipate or determine allocation easily, and the use of varying block sizes was therefore deemed unnecessary. In order to preserve blinding of the study researcher, randomisation will be conducted by a third party not involved in assessing or treating the participants, and this third party will also inform the therapist, who will be responsible for informing participants of their allocation.

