### Sample size calculation for phase III efficacy trial

Power and sample size calculations were based on testing the primary question of the efficacy of guided internet-RFCBT in terms of reducing the onset of major depression relative to the no-intervention control. For our primary comparison of guided i-RFCBT versus the no-intervention control, the Topper et al. study using the binary outcome of number of individuals meeting caseness for depression at 12 months, reported 13.1 % incidence of depression in guided i-RFCBT and 32.2 % incidence in the no-intervention control (hazard ratio = 0.41). Assuming similar effect sizes to the Topper et al. study for our intended time-to-outcome survival analysis over 12 months, then to detect the hazard ratio of 0.41 between these arms at the two-tailed 5 % alpha level, 75 participants must be recruited to each arm to provide 86 % power.

Estimates for change in depressive symptoms pre-to-post intervention for the guided i-RFCBT relative to the waiting list control indicate that 78 participants per arm provide a power of 80 % to detect the observed effect size of d = 0.51 from the Dutch trial at the two-tailed 5 % alpha level, allowing for the 20 % follow-up drop-out attrition observed in the Dutch study.

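### The primary Cox model commits only to condition: whether the two stratification factors enter is left open and baseline depression severity is not named, so the primary hazard ratio is not fixed in advance and some power may be lost

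*Protocol article*

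**What the plan says.** All references are to the Protocol article.

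- **Primary model** (Statistical analysis plan for phase III efficacy trial). Cox regression for onset of major depression: "Although condition will be the main independent variable included in the model, we will also consider sex and history of past depression". A parenthesis identifies these two as the stratification variables. Baseline depression severity is not mentioned for this model.
- **Randomisation** (Randomisation and allocation concealment). "Randomisation will be stratified by sex and by past history of depression", the latter as present or absent.
- **Symptom and rumination/worry ANCOVAs** (same analysis section, next paragraph). These are specified "with baseline symptom levels and stratification variables as covariates".
- **Time to generalized anxiety disorder** (same paragraph). Cox regression, with no covariates stated.
- **Data available** (Telephone screening and baseline assessment). The PHQ-9 is completed at baseline.
- **Prognosis** (Study aims and objectives). Earlier depressive episodes are described as a major risk factor for another one. No effect size is given.

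**The concern.** The wording on the primary model does not commit. *Consider* could mean that sex and past depression enter as main effects, that they define strata with separate baseline hazards, that they are tested as interactions, or that they enter only if they seem useful. The interaction reading is a live one: the randomisation section gives studying differences by sex and by first onset versus relapse as a purpose of the stratification, and the section on mediation and moderation lists the stratification variables as possible moderators. Each choice gives a somewhat different hazard ratio and p-value.

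Two things are at stake. First, with few events expected, a choice of covariates made after results are seen could decide significance. Second, if the factors are left out, the analysis ignores the balance that stratified randomisation created. The unadjusted standard error is then slightly too large, and information from prognostic covariates is not used.

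**Working it through.** **1. The plan's own power figure.** The plan sets out "to detect the hazard ratio of 0.41 between these arms at the two-tailed 5 % alpha level" and says "75 participants must be recruited to each arm to provide 86 % power". The incidences are 13.1% (guided) and 32.2% (control), over 12 months.

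- Events from the stated incidences: 75 × (0.131 + 0.322) = 34.0.
- Events from 32.2% and HR 0.41: the guided risk is 1 − 0.678^0.41 = 0.147, so 75 × (0.147 + 0.322) = 35.2.
- Schoenfeld power = Φ(½·√E·|ln HR| − 1.96). With E = 34.0: ½ × 5.83 × 0.892 − 1.96 = 0.64, which gives 73.8%. With E = 35.2: 75.3%. Freedman's form gives 68–70%.

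The 86% is not reproduced at the stated inputs. That is a separate matter. Here it means only that there is little power to spare.

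**2. Events per parameter.** At 75 per arm over 12 months there are about 34 events. At 78 per arm over 15 months, with a constant hazard and HR 0.41, the control risk is 1 − 0.678^1.25 = 0.385 and the guided risk is 1 − 0.678^(1.25 × 0.41) = 0.181, so 78 × 0.565 ≈ 44 events. Four parameters (condition, sex, past depression, PHQ-9) have 34/4 = 8.5 to 44/4 = 11 events each. Three parameters (without PHQ-9) have 11.3 to 14.7. Both counts ignore dropout. If the 20% attrition (stated only for the symptom-score calculation) removed those participants' information entirely, 60 per arm would give 60 × 0.453 = 27.2 events, or 6.8 per parameter.

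**3. Effect of adjustment on power.** The documents give no prognostic effects, so all of the following are assumptions: exponential times, 75 per arm, 12 months, no dropout, control risk 32.2%, conditional HR 0.41, arms balanced on strata, 75% in one sex, 50% with past depression. There were 3,000 trials per row (Monte Carlo standard error about 0.9 points). The assumed hazard ratios are for sex / past depression / one SD of PHQ-9.

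| Assumed prognosis | Large-sample HR: unadjusted → strata → strata + PHQ-9 | Power (%), same order | Full gain | Gain of PHQ-9 over strata |
|---|---|---|---|---|
| None (1 / 1 / 1) | 0.413 → 0.413 → 0.413 | 69.7, 70.2, 70.2 | 0.5 (noise) | 0 |
| Moderate (1.2 / 1.7 / 1.3) | 0.421 → 0.418 → 0.414 | 70.1, 71.4, 72.2 | 2.1 | 0.8 |
| Strong (1.5 / 2 / 1.5) | 0.430 → 0.423 → 0.415 | 68.4, 70.3, 72.1 | 3.7 | 1.8 |
| Very strong (1.5 / 3 / 2) | 0.452 → 0.442 → 0.412 | 62.3, 65.6, 72.6 | 10.3 | 7.0 |

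**4. A second set of assumptions.** 78 per arm, 15 months, 20% dropout spread uniformly, 70% female, sex HR 1.3, 50% with past depression. With past-depression HR 2 and PHQ-9 HR 1.5 per SD, power is 73.4, 74.5 and 77.0% (gain 3.6). With 3 and 2.0 it is 68.2, 72.2 and 78.6% (gain 10.4). These pairs of effects match the strong and very strong rows above, and the gains agree.

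**5. Under the null.** In the second set-up, with effects 3 and 2.0, the unadjusted test rejects in 3.9% of trials against 4.9% for the adjusted test. With 3,000 trials the standard error is √(0.05 × 0.95/3000) = 0.4 points. The unadjusted test is mildly conservative, and there is no inflation of type I error.

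**The case against.** **The word may simply mean inclusion.** Read naturally, condition is the main term and the strata enter beside it. This stands. A reader might infer that the primary hazard ratio is attenuated and that power is lost. The text supports only the conditional statement: if the factors are left out, some power goes.

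**The shift in the hazard ratio is not bias.** This also stands. A marginal and a conditional hazard ratio are different quantities, and an unadjusted Cox model in a randomised trial is valid. The design value of 0.41 accompanies crude incidences, so it is closer to an unadjusted figure. The move to 0.42–0.45 is largely non-collapsibility. The power loss and the open choice do not depend on that argument.

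**The secondary models do not all adjust.** Correct. Only the ANCOVAs commit to both kinds of covariate; the Cox model for generalized anxiety disorder names none. Moreover, an ANCOVA adjusts for the baseline of its own outcome, and time to onset has no such baseline. The differing treatment is therefore not a contradiction, and a sparse model on few events is defensible.

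**The sizes are assumed.** They are. Screening also excludes PHQ-8 scores of 15 or more, which narrows the severity range and makes a hazard ratio of 2 per SD an extreme case.

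**A covariate list belongs in the full analysis plan.** This is partly right, and the absence of detail alone would be no finding. But the article does take up the primary model's covariates, under an analysis-plan heading, and settles them less firmly than the ANCOVAs' covariates. That wording can be criticised as it stands.

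**Conclusion.** The point holds as one about an unfixed primary model. The article binds the primary Cox model to condition only, leaves the role of the two stratification factors open, and does not name a baseline severity measure that is already collected.

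The size is modest. Leaving out all three covariates costs about 2 to 4 power points under moderate to strong assumed prognosis, about 10 only with very strong predictors, and nothing if they are not prognostic. If the strata are in fact included, adding PHQ-9 is worth about 1, 2 and 7 points in the moderate, strong and very strong cases. The freedom to choose the primary estimate after seeing results remains whatever the prognostic strength.

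The documents do not support saying that the hazard ratio is biased, that power is certainly lost, or that there can be no reason for a sparse model. The firm part is to commit to the stratification factors. Baseline PHQ-9 is a recommended addition whose value depends on effects the documents do not quantify.

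**What to change.** Replace the non-committal sentence with a commitment: the primary estimate is the guided-versus-control hazard ratio from a Cox model with condition, sex, past depression (yes/no) and continuous baseline PHQ-9; the unadjusted model is reported as supportive. Keep interaction terms with the stratification variables in the moderation analysis, outside the primary model.

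The cost is one sentence and no new data. The reported hazard ratio becomes a conditional one and should be labelled so, and four parameters rest on roughly 8.5 to 11 events each, fewer with dropout. If that is judged too many, sex and past depression are the minimum set, and the reason for leaving out PHQ-9 should be stated. Recruitment was ongoing when the article was submitted, so this could be settled before outcomes are analysed.
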